*Experiment B: Does action improve sensitivity to backwards-masked stimuli?* This experiment combines MIB with a type of backward masking of the target stimulus. If the target is backwards-masked to preclude perception in the passive condition—by removing the target as it approaches the foveal region of the visual field—AI-C predicts that the target will still be perceived when the same masking setting is applied in the active condition. If there is no difference between conditions, or if the passive condition results in improved perceptual recognition, this would be evidence against AI-C; otherwise, this will provide evidence that action facilitates conscious awareness, and in that sense will predominantly support the active inference prediction.

Both experiments will also be equipped with measures of autonomic and neuromodulatory (i.e., cardiac and pupil) activity to adjust for any differences in attentional set (e.g., arousal) that could be considered to confound condition-specific differences. Further, in primates, attentional selective sampling under normal conditions is typically associated with motor activity (e.g., ballistic saccades or microsaccades, as well as eye blinks and pupil dilation and constriction), and therefore this study will record not only the saccades in the active condition (for play-back in the passive condition) but also microsaccades, pupil diameter and blinks throughout, in order to quantify differences between two conditions (such as microsaccades when fixating on the relevant location in both the passive and action conditions).

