1)Replay periods are epoched using a window extending from the initialization of the cue to the first fixation on the target stimulus.2)Any values outside of the boundaries of the screen are removed, and eyeblink periods must be linearly interpolated between points in order to maintain a smooth replay. Any datapoint more than 1.5° of visual angle away from the linear path from fixation to target will not be considered in the replay. Any datapoint more than 1.5° away from the previous data point is considered an error and will not be considered in the replay.3)Any trials containing poor signals (i.e., missing more than 20% of sample points in both eyes; [41]) will not be selected for replay. For replays that meet this standard all non-included samples will be linearly interpolated. To ensure equal numbers of active and passive trials, active trials may be used in replays additional times after running through all available replays. The replay path corresponding with the target stimuli will be used for replay if available, but the path trajectory will be transformed across randomly selected polar angles.

***Analysis.*** The following pre-processing steps describe the post-experiment analysis of eye tracking data for use in trial validation, eye-blink, microsaccade and pupillometry measures:

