1)Trials in which participants fail to maintain 1.5 seconds of fixation within the allowable time period (20 seconds) are removed.2)Any values outside the screen boundary are removed and eyeblink periods are linearly interpolated based on the surrounding data points. Eye blinks are defined by pupil size > 1.5 standard deviations below or 2 standard deviations above participants average pupil size.3)Microsaccades will be quantified for each trial based on the microsaccade detection procedure defined by Engbert [42].4)Trials are epoched using a window time-locked to the cue and first fixation on a target stimulus for both eye-gaze location and pupil size. The window therefore extends before these events (to encompass the fixation, cue, and subsequent movement) and after these events. In Experiment B, the window will be extracted time-locked to the cue and the onset of the mask.5)Trials containing poor quality signals will be removed from subsequent analysis. Poor signal quality is defined as trials missing more than 30% of samples from both eyes [41]. Trials will also be rejected if the participant fails to fixate on a target stimulus or if the participant fails to maintain a central fixation in the passive condition during the period between the cue and the end of the movement sequence.

**3. Electrocardiogram.** To track physiological arousal during task performance, we will measure changes in heart period (i.e., inter-beat interval) derived from the electrocardiogram (ECG). We will acquire the ECG from a modified Einthoven lead-II configuration using either an ADInstruments PowerLab 26T device (MELBOURNE) or by a modified lead-I (clavicular) configuration using a BIOSEMI ActiveTwo EEG amplifier (JENA) and Biosemi flat active electrodes. Inter-beat intervals will be quantified as the duration between successive R-peaks (RR intervals). R-peaks will be identified using an automated QRS detection routine based on the Pan-Tompkins algorithm (e.g., [43]). Physiologically implausible inter-beat intervals (< 300 ms or > 2000 ms) will be rejected, as will any remaining intervals > 4 standard deviations from the participant’s mean. Missing intervals will be corrected via cubic-spline interpolation.

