### Planned analyses and expected outcomes

In order to capture the contribution of covariates within both experiments, 3A and 3B dependent variables will be analysed under a generalized linear modelling framework based on a pre-specified decision tree (see Fig 3). The choice of link-function will be informed by the distributional properties of the data and the evaluation of standard model diagnostics (e.g., Q-Q plot of residuals) and indices of marginal likelihood (e.g., AIC). Nested model comparison will be used to evaluate whether model fit is significantly improved by the inclusion of focal parameters. Random effects and additional covariates accounting for potential sources of noise (e.g., mean inter-beat interval, time-on-task) may be included if warranted by theoretical considerations and model comparisons (for a similar approach, see [44]). As part of this analysis we will quantify microsaccades frequency and latencies, as well as pupil area trajectory. These findings will be included in the results and, if we find that any of these data features, when considering the period immediately following the cue, differ significantly between conditions we will include these as covariates in the model.

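### The blink rule is a pupil-size cut that labels ordinary constriction and dilation as blinks, at a rate that depends on condition whenever pupil size does

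*Protocol article*

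**What the plan says.** The rule stands in Data collection procedures, 2. Eye-tracking, in the numbered list under Analysis. Step 2 reads "Any values outside the screen boundary are removed and eyeblink periods are linearly interpolated based on the surrounding data points", followed by the definition "Eye blinks are defined by pupil size > 1.5 standard deviations below or 2 standard deviations above participants average pupil size". Nothing is said about tracker-reported signal loss, duration or rate of change. Nor does the text say whether the mean and SD are taken before or after samples with no pupil signal are removed.

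The list is introduced as "post-experiment analysis of eye tracking data for use in trial validation, eye-blink, microsaccade and pupillometry measures", so the same step defines the blink measure and prepares the pupil and microsaccade measures. Step 3, after the interpolation, is "Microsaccades will be quantified for each trial based on the microsaccade detection procedure defined by Engbert".

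The uses are stated in two places. The Introduction (Current study) says the study records "microsaccades, pupil diameter and blinks throughout, in order to quantify differences between two conditions". Planned analyses and expected outcomes says "we will quantify microsaccades frequency and latencies, as well as pupil area trajectory". That section also gives the rule by which these features become model covariates: "if we find that any of these data features, when considering the period immediately following the cue, differ significantly between conditions we will include these".

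**The concern.** When the lid closes, the tracked pupil shrinks or disappears. A cut on pupil level with no other criterion also catches an open eye that happens to be constricted or dilated. The upper arm has no blink rationale: a pupil more than 2 SD above average is a large pupil, and dilation is the arousal response that the pupil record is meant to capture.

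Three things are at stake. First, the blink measure contains false blinks. Because the cut-offs are tied to the participant's average, their rate differs between active and passive trials whenever pupil size differs, so a blink difference may only restate a pupil difference. Second, the pupil trace loses its extremes before conditions are compared. Third, microsaccades inside flagged stretches may be lost if gaze is interpolated as well as pupil size, because detection is listed after this step.

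Operational hypotheses gives motor-associated arousal as NREP's account of an active advantage, and the Discussion treats pupil change as the stimulus-bound measure, with inter-beat interval covering context-specific arousal. Pupil quality therefore bears on a rival explanation that the study wants to address.

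**Working it through.** **Inputs.** From the document: cut-offs of -1.5 SD and +2 SD about the participant's average; flagged periods linearly interpolated; 1000 Hz sampling; equal numbers of active and passive trials. Assumed, because the document gives no figure: normally distributed open-eye pupil size; condition differences of 0.2 to 1.5 within-condition SD; blink samples coded as zero making up 2% or 5% of samples; open-eye coefficient of variation (CV) of 10-20%. The document states no flagging rate, so there is no figure of its own to reproduce.

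**1. Flagging with no blinks at all, mean and SD from valid samples.** P(Z < -1.5) + P(Z > 2) = 0.0668 + 0.0228 = 0.0896, or 9.0%. Heavier tails (t with 5 or 10 df) give 8.0-8.7%; a uniform shape gives 6.7%. For contrast, the article's ECG rule uses absolute limits and then a 4 SD cut, which takes 2 × P(Z > 4) = 0.006% of normal values.

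**2. If zero-coded blinks stay in the mean and SD.** Set the open-eye mean to 1, CV = c and blink share = b. Then mean = 1 - b and variance = (1 - b)(1 + c²) - (1 - b)². With b = 2% and c = 15%, the mean is 0.98 and the SD 0.204. The cut-offs then lie at -2.17 and +2.59 open-eye SDs, and 2.0% of ordinary samples are flagged. With b = 2% the share is 0.3% at c = 10% and 3.8% at c = 20%. With b = 5% it is 0-1.1% over c = 10-20%. The range is therefore about 0-9%, depending on a choice that the text leaves open.

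**3. Dependence on condition.** Place the two conditions at +d/2 and -d/2 around the participant's mean, each with SD 1. The pooled SD is s = √(1 + d²/4), and the band runs from -1.5s to 2s. For d = 0.5, s = 1.031 and the band is (-1.546, 2.062).

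- Larger pupil: P(Z < -1.796) + P(Z > 1.812) = 0.0362 + 0.0350 = 7.1%.
- Smaller pupil: P(Z < -1.296) + P(Z > 2.312) = 0.0975 + 0.0104 = 10.8%.

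For d = 1, s = 1.118 and the band is (-1.677, 2.236).

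- Larger pupil: 0.0147 + 0.0413 = 5.6%.
- Smaller pupil: 0.1196 + 0.0031 = 12.3%.

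The smaller-pupil condition gets more false blinks because the lower cut is the tighter one.

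**4. Shrinkage of the pupil difference, same band.** In a smooth trace, an excursion past a cut is bridged from samples near that cut, which roughly caps it. Dropping flagged samples is shown for comparison; the text does not prescribe it.

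| True difference (SD) | Lost if capped | Lost if dropped |
|---|---|---|
| 0.2 | 8.9% | 33.6% |
| 0.5 | 8.4% | 32.0% |
| 1.0 | 6.9% | 27.1% |
| 1.5 | 5.3% | 21.2% |

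**The case against.** The strongest reply is that the rule is identical in both conditions, and that its effect on the pupil difference is small. The second half stands: capping leaves 91-95% of the difference. The first half does not, because a common rule with a participant-wide band still gives unequal false-blink rates once pupil size differs (step 3).

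Some stronger readings are tempting, and the document does not support them.

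- A reader might infer that about a third of a pupil difference is lost. That figure belongs to deleting flagged samples, whereas the text interpolates.
- A reader might infer that whichever condition shifts pupil size loses more samples. With the band on the participant's overall average, the smaller-pupil condition loses more, so a condition that dilates the pupil loses fewer.
- A reader might infer that the arousal check is biased towards finding nothing. The entry rule is a significance test. Capping reduces spread as well as the mean difference, so the effect on the test is not established.
- A reader might infer that arousal is otherwise unchecked. Heart period is recorded for that purpose, appears as a candidate covariate, and is untouched by this rule.
- A reader might infer direct damage to the primary outcomes. Time to reappearance and boundary radius do not depend on pupil size, and blink count is not among the features named for covariate entry.

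It is also fair to say that the 9.0% is an upper-end figure under stated assumptions, and that microsaccade loss depends on gaze being interpolated too, which the text suggests but does not state.

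**Conclusion.** The point holds as a defect in a stated pre-processing rule. Followed as written, it mislabels between about 0% and 9% of ordinary samples as blinks. The upper figure rests on normality and on a mean and SD from valid samples; the lower on zero-coded samples inflating the SD. Because the text leaves that choice open and Status and timeline has each lab build its own pipeline, the two sites could apply the rule differently.

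The clearest consequence is for the blink comparison: 10.8% against 7.1% false flags at a 0.5 SD pupil difference, and 12.3% against 5.6% at 1 SD, at the upper-end base rate. Attenuation of the pupil difference is modest, about 5-9%, and would reach 21-34% only if flagged samples were dropped. The consequence for the primary models is indirect, through which pupil and microsaccade covariates enter and how well they adjust. The change should be made, but the flaw does not undermine the main contrasts.

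**What to change.** Define a blink by loss of the pupil signal (tracker blink events, or zero or missing pupil samples), with fixed padding on each side and a pupil-velocity criterion for partial blinks. Remove both arms of the SD rule. For microsaccade detection, mark these periods as excluded rather than interpolating across them. Put the same definition in both labs' pipelines and timestamp it through the route in Dealing with amendments, before any active-passive comparison of eye measures is run.

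The cost is minor recoding of offline pre-processing at both sites. Data collection does not change, and because the data-sharing plan covers unprocessed data, the new rule can be applied to recordings already made.

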### Experiment A: Time to reappearance following motion-induced blindness

**Design, stimuli, and procedure.** This experiment deploys a within-subjects design to contrast differences in the time to reappearance of stimuli rendered subjectively invisible by MIB. The MIB task will be performed in conjunction with eye tracking in order to produce both active looking blocks and passive viewing blocks (where the active gaze is precisely replayed).

We will use the Racially Diverse affective expression (RADIATE) face stimulus set [37]. We use only neutral faces for our stimulus set, removing any stimuli with accuracy ratings for neutral emotional state below 80%. This leaves 108 stimulus images of distinct identities (and one used solely for instructional purposes). On each trial, the stimuli will be pseudo-randomly sampled with a constraint that no greater than two consecutive repetitions of a specific identity will be shown to participants. Each target stimulus will be converted to greyscale, scaled to 200x200 pixels, and luminance-matched using the SHINE toolbox [38]. All images will be enclosed in an elliptical mask centred on the face shape. In order to correct the luminance difference created by the mask the luminance of each stimulus image will be scaled to match an RGB value of 100 (+/- 0.1%); the background colour of the display will also be matched to this value.

Target stimuli will be presented at a randomly-selected polar angle (1–360 degrees) 9 degrees of visual angle from central fixation. In each trial, a blue central fixation dot will be present behind the stimulus and a cross pattern filling the entire screen will rotate at 2.7s/cycle, in line with previous work [39]. As the target in this design will either (in the passive case) remain stationary after being moved into central fixation or (in the active case) be foveated by the participant, it will ultimately fill the centre of the visual field in both conditions. This means that central attentional resources will eventually be allocated to it, and it will become visible even in the passive condition. This is consistent with active inference, since attention is a (covert) form of action. However, the thrust of this experiment lies in the role of overt action (eye movement), recognizing that covert attentional resources are also deployed in the passive condition at some point in the task.

Experiment A sessions will be separated into three sections:

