*Main experiment*. Following the successful completion of training and practice trials, participants will be reminded (via diagram) how to complete active and passive trials before the main experiment begins. Participants will be informed that a cue in the active trial will allow them to move their eyes to look at the location where the target was previously seen; in contrast, in the passive trials the cue is an instruction to maintain fixation. During each experimental trial, the participant will be initially required to perform an uninterrupted fixation on a central dot for at least 1.5 seconds before responses can be given. If the participant is unable to maintain eye gaze on the target for more than 1.5 seconds, they will not be able to complete the trial. If the participant looks at the peripheral target stimulus during this time period, the trial will automatically end (and will not be counted as a valid trial). The participant will then be asked to press a button when the peripheral target stimulus entirely disappears; following this response, after a short delay (randomly jittered between 500ms-1000ms) a cue will be given to signal the next phase by flashing a different colour of the central fixation. In the active trial block, after the cue, the participant will be asked to look to the target location. In the passive block, participants will be told to maintain central fixation while the entire visual display (including the rotating grid) moves in relation to the fixation cross to eventually position, in an exact replay, the stimulus as it was in a randomly selected trial from the active block. Crucially, in this version of the experiment participants will be asked to respond as soon as they become aware of the target, thereby generating an estimate of the time to reappearance.

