An important factor, considered in the development of this study protocol, is the potential contribution of arousal in eliciting or promoting awareness, where arousal can take the shape of either phasic (stimulus-specific) or tonic (context-specific) arousal. In basic physiological terms, the role of arousal in psychophysical experiments such as those described here is well understood—specifically, that it enhances neural excitability and, depending on the level, may increase signal-to-noise ratios. Here, the locus coeruleus (LC) system mediates tonic and phasic arousal states affecting overall alertness, while phasic arousal helps fine-tune perception in response to specific stimuli. Studies using pupillometry have directly linked LC activity to changes in sensory processing, reinforcing the idea that arousal plays a major role in perception. All theories should thus expect these physiological processes to be in play, and understood as such the presence of arousal will not directly support one theory over the other. It will be a matter of further interpretation and modelling of the results to specify how arousal aligns with the core tenets of each theory. Here, it is of significance that, according to the active inference framework, arousal in this setting can be read in terms of attentional set and therefore reflects mental active inference, usually involving interoceptive inference [45–51]; this would make the arousal process an indispensable part of the active inference underpinning a change in consciousness. In contrast, for IIT and NREP, arousal would pertain to processes distinct from but interacting in important ways with the core processes posited by NREP and IIT as necessary for consciousness; this difference in outlook on arousal and attention partially explains the differences in the prediction table (shown above) for this experiment; that is, IIT and NREP’s predictions are not the opposite to those of AI-C, but partially overlap, and with weaker confidence. The interpretation of results, in particular differences of arousal between the two conditions, in the light of theoretical commitments will thus help situate the role of arousal and attentional set in diverse theories of consciousness. To help disambiguate the contributions of motor active inference (saccades) and mental active inference (i.e., attention and arousal) to perception, we opted to measure cardiac and pupil responses. Measuring inter-beat interval estimates allows us to adjust for context-specific arousal for a given trial. Pupillometric changes are considered integral to stimulus-bound aspects of active inference [51–53]. Cardiac and pupil data therefore allows us to quantify the contribution of (stimulus-specific and context-specific) attentional set and (saccadic) motor action to changes in perceptual content.

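### Pupil area is compared between conditions after the cue with no gaze-position correction, although only active trials move the eye up to 9° off-centre, so the covariate test can be positive without any arousal difference.

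*Protocol article*

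**What the plan says.** All references are to the protocol article.

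- **Target position** (Experiment A, design, stimuli and procedure): "Target stimuli will be presented at a randomly-selected polar angle (1–360 degrees) 9 degrees of visual angle from central fixation".
- **Active trials** (Experiment A, main experiment): "In the active trial block, after the cue, the participant will be asked to look to the target location".
- **Passive trials** (same place): "In the passive block, participants will be told to maintain central fixation while the entire visual display (including the rotating grid) moves".
- **Trial rejection** (Data collection procedures, item 2 Eye-tracking, Analysis, step 5): "Trials will also be rejected if the participant fails to fixate on a target stimulus or if the participant fails to maintain a central fixation". The central-fixation requirement is for the passive condition, from the cue to the end of the movement.
- **Pupil epoch** (same list, step 4): "Trials are epoched using a window time-locked to the cue and first fixation on a target stimulus for both eye-gaze location and pupil size". The window runs before and after both events. In Experiment B it is locked to the cue and to mask onset.
- **Use of the measure** (Planned analyses and expected outcomes): pupil area trajectory is quantified. Eye features become model covariates if they, "when considering the period immediately following the cue, differ significantly between conditions".
- **Purpose**: Current study says the cardiac and pupil measures serve to adjust for attentional set such as arousal. The Discussion adds: "Cardiac and pupil data therefore allows us to quantify the contribution of" attentional set and saccadic motor action to changes in what is perceived.

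The analysis list covers fixation failure, screen bounds, blinks, microsaccade detection, epoching and signal quality. It has no step for gaze position. The tracker is desk-mounted about 55 cm from the eye and the head is on a chin rest; the camera angle is not given.

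**The concern.** The replay matches what falls on the retina. It does not match the direction in which the eye points, and that direction sets the apparent size of the pupil in a fixed camera. Off-centre gaze after the cue coincides with condition, and the trial-rejection rule enforces this.

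A pupil difference between conditions can therefore arise from geometry alone. Two uses are affected. The reported active-passive pupil comparison would be partly a gaze effect. On average this makes the active pupil look smaller, so it could hide a real movement-related dilation or suggest a false reduction. The significance rule could also put into the outcome model a covariate that carries condition itself, which can distort the active-passive estimate for reappearance time or masking radius. Arousal that accompanies movement is the explanation that neurorepresentationalism offers for an active advantage (Operational hypotheses), so the measure bears on how the theories are compared.

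**Working it through.** **1. The plan's own figure.** The protocol adopts 55 participants, citing at least 80% power at partial eta squared 0.13. Take a within-subject F(1, n−1) test at two-sided alpha 0.05 (assumed). Then f² = 0.13/0.87 = 0.149, and power at n = 55 is 0.804 with noncentrality n·f², or 0.797 with (n−1)·f². The figure reproduces. It is used below only as n.

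**2. Foreshortening after landing.** Assume that apparent area is proportional to the cosine of the angle between gaze and camera axis. For camera elevation c below the line of sight and target direction φ, measured from the camera's direction, area relative to central gaze is

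ratio = [cos 9°·cos c + sin 9°·sin c·cos φ] / cos c = cos 9° + sin 9°·tan c·cos φ.

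Over uniform polar angles cos φ averages zero, so the mean change is cos 9° − 1 = −1.23% at any c (about −0.6% in diameter). Passive trials have zero expected change. Single-trial values depend on c, which is assumed:

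| c | Minimum | Maximum | SD |
|---|---|---|---|
| 10° | −4.0% | +1.5% | 2.0% |
| 20° | −6.9% | +4.5% | 4.0% |
| 25° | −8.5% | +6.1% | 5.2% |

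**3. Dilution by the pre-saccade period.** Until the saccade starts, gaze is central in both conditions. With window W, assumed latency 150–300 ms and assumed flight time 45 ms, the share on target is (W − latency − 0.045)/W, and the mean shift is −1.231% times that share.

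| W | Share on target | Mean shift |
|---|---|---|
| 0.5 s | 31–61% | −0.38% to −0.75% |
| 1 s | 66–81% | −0.81% to −0.99% |
| 2 s | 83–90% | −1.02% to −1.11% |

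The protocol does not fix W. In Experiment B, gaze at mask onset is short of the target centre by the boundary radius r. The mean shift at that moment is about cos(9° − r) − 1, smaller than 1.23% but still not zero in active trials.

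**4. Chance that the covariate rule fires with no arousal difference.** This uses a paired t test with n = 55, 54 degrees of freedom, two-sided 0.05, and m = 72 trials per condition (the same section later gives 144 of each type). The SD of a participant's difference is √(s_b² + 2·s_t²/m) and the noncentrality is shift/SD·√55. Example: shift 0.9%, s_b = 2%, s_t = 10% gives SD = √(4 + 2.78) = 2.60, noncentrality 2.56 and probability 0.71. All SDs are assumptions. Ranges are for s_t from 15% down to 5%:

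| Mean shift | s_b = 1% | s_b = 2% | s_b = 4% | s_b = 6% |
|---|---|---|---|---|
| 0.4% | 0.191–0.610 | 0.149–0.270 | 0.095–0.110 | 0.073–0.077 |
| 0.6% | 0.368–0.919 | 0.276–0.523 | 0.153–0.188 | 0.103–0.111 |
| 0.9% | 0.682–0.999 | 0.535–0.857 | 0.285–0.361 | 0.172–0.191 |

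Every cell exceeds 0.05, some only slightly.

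**5. Why linear gaze regression fails.** Horizontal and vertical gaze offsets both average zero over random polar angles, in active as in passive trials. Linear terms can absorb the sin 9°·tan c·cos φ part but not the constant. Fitting intercept, x and y to the geometry in step 2, with one central passive trial for each active trial, leaves an active-passive residual difference of −1.23% at both c = 10° and c = 20°, which is the whole mean artefact.

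**The case against.** The strongest reply is that gaze-position correction is pre-processing detail that an article leaves to the preregistration and the laboratories' pipelines, neither of which is shown, and that an effect near 1% is minor. Part of this stands. The effect is small, it applies only after the saccade, and without variance figures its practical weight is uncertain. But the article does set out the pre-processing steps, the epoch and the decision rule. Followed as written, these give a comparison aligned with gaze position.

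Three stronger readings are tempting and not supported.

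- **That the 9° saccade contaminates the microsaccade counts.** Current study lists the instructed saccades separately from microsaccades and gives as its example a comparison during fixation in both conditions. Nothing says that the instructed saccade would be counted.
- **That the study could then not separate motor action from arousal.** The Discussion also relies on inter-beat interval, which gaze direction does not affect, and says that arousal does not directly favour one theory. The predictions in Tables 1 and 2 concern reappearance time and masking radius, not the pupil.
- **That the bias is 1.2% throughout, or as large as the single-trial extremes.** The first figure holds only after landing. The extremes need an assumed camera angle, and their directional part averages out.

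A remedy that simply cut the window at movement onset would also meet a fair objection: it would drop the movement-related arousal that the rival account invokes.

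**Conclusion.** The point holds for pupil area. With equal arousal, the plan as written is expected to record a smaller pupil in active trials: 1.23% after landing and about 0.4% to 1.0% over a 0.5 to 1 s post-cue window, with less at mask onset in Experiment B. The post-landing figure rests on cosine foreshortening and random target angles, and the window averages also on assumed saccade timing. The sign is that of the expected value; a finite set of random angles adds scatter. The covariate rule can fire on this alone. For shifts of 0.4% to 0.9% its chance ran from about 0.07 to nearly 1.00 across the assumed SDs, so no single error rate can be claimed. The behavioural outcomes themselves are not affected. What is affected is the pupil comparison and any model that the pupil covariate enters.

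**What to change.** Add a step to the eye-tracking analysis: before the between-condition comparison and before any use as a covariate, correct pupil area for gaze position by one of two routes.

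1. A geometric (cosine) model that uses the camera position measured at each site.
2. A per-participant map of pupil area against gaze position, estimated from the central and 9° peripheral fixations in the training phase of both experiments. There, gaze position is not tied to condition.

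State that linear regression on horizontal and vertical gaze alone does not suffice. Give the length of the post-cue window. Report the uncorrected window from cue to movement onset (saccade onset in active trials, replay-motion onset in passive trials) only as a sensitivity check, because it misses movement-related arousal.

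The cost is small: wording and script, one camera measurement per site for the first route, and retention of the training-phase samples for the second. The downside is slightly more analysis work and some model error in the correction.
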